### Randomization and blinding

Each participant will be assigned a unique ID number by the research assistant during the screening/baseline assessment. Randomization will occur at the individual AYA level and be stratified by site. Following the determination of eligibility and completion of the baseline assessment, the research assistant will communicate the ID number to a study staff based at research headquarters who will not interact with study participants. This study staff will maintain a randomization sequence that will be developed a priori by a US-based research staff. This list will not be available or viewable to data collectors in Zambia. The list will have a sequence of treatment assignments (CETA or T-CETA or TAU) in random order, stratified by site, produced via a random number generator in Microsoft Excel. Randomization will be imbalanced (1.5 CETA: 1.5 T-CETA: 1 TAU) due to the different sample size requirements in the TAU control arm (see the “Data analysis” section). Eligible AYA participants will be assigned a condition based on the next available slot on the randomization list and inform the field staff of the assignment. At this point, the field staff will not be blinded to condition assignment for participants they assess. Eligible AYA clients will be informed immediately of the result of the randomization and appropriate next steps: CETA and T-CETA participants will be told that a counselor will be contacting them within 48 h to set up the first session; TAU participants will be told that the study team will contact them in approximately 3 months to schedule their first post-assessment. The use of ACASI will result in the outcome assessments being blinded; data analysts will also be blind to the intervention status when conducting analyses. Due to the nature of the intervention, neither counselors nor AYA clients will be blinded.

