### Data analysis

The analysis will be done using an intent-to-treat approach. Mixed effects regression models will be estimated for each mental/behavioral health outcome. Models will include fixed effects of treatment group, time, and a group × time interaction term. Random effects will include client ID and counselor ID. There will be two sets of analyses. First, we will conduct a superiority analysis, in which each of the CETA arms (CETA and T-CETA) is separately compared to TAU. Second, we will conduct a non-inferiority analysis in which we will compare the outcomes between the CETA and T-CETA groups.

The total number of AYA participants will be *N* = 400. We conducted power calculations for each of the three primary outcomes for which AYA will be enrolled in the study (trauma symptoms, internalizing symptoms, externalizing behaviors). All three required similar sample sizes; trauma symptoms required the largest sample size and are presented here. Based on a previous study with AYA using the same trauma symptom scale as this study (CPSS) [73], we hypothesize a baseline mean value of approximately 19.0 and a standard deviation of 13. For the superiority analyses, in which we will separately compare each CETA condition (in-person CETA and T-CETA) to the TAU control, we will assume an alpha = 0.025 to account for two comparisons. Further assuming power = .80 and an expected minimum effect size of each CETA condition compared to TAU of 0.5, we would require 78 persons per arm. For the non-inferiority analysis, in which we will compare the two CETA conditions to each other, we assume an alpha = 0.05, power = 80%, and a non-inferiority margin of 4.7, which is equivalent to one-third of the anticipated standard deviation. Previous studies have indicated that differences in the outcomes that are less than one-third of the standard deviation are considered not practically meaningful. Based on these assumptions, we would require 114 in each CETA arm for the non-inferiority comparison. Using the more conservative estimate for the CETA conditions (*N* = 114 each) and the estimate for the TAU (*N* = 78) yields a total sample size of *N* = 306. Assuming 20–25% attrition based on previous studies, we have inflated the final sample size to *N* = 400 (*N* = 100 TAU, *N* = 150 CETA, *N* = 150 T-CETA).

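### The non-inferiority margin (4.7), the SD (13), the one-third-SD rule and the 114 per arm do not agree with one another

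*Protocol article*

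**What the plan says.** All the figures are in the Data analysis section of the protocol article, in the paragraph on sample size. It works with trauma symptoms on the CPSS, the primary outcome said to need the most participants.

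- SD: "we hypothesize a baseline mean value of approximately 19.0 and a standard deviation of 13".
- Margin: "non-inferiority margin of 4.7, which is equivalent to one-third of the anticipated standard deviation".
- Reason for the margin: earlier studies are said to show that "differences in the outcomes that are less than one-third of the standard deviation are considered not practically meaningful".
- Error rate and power for this comparison: "we assume an alpha = 0.05, power = 80" per cent. Whether alpha is one-sided or two-sided is not stated.
- Result, presented as following from these inputs: "we would require 114 in each CETA arm for the non-inferiority comparison".

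The two CETA arms are equal in size (the Randomization and blinding section has "Randomization will be imbalanced (1.5 CETA: 1.5 T-CETA: 1 TAU"). After allowance for 20–25% attrition, 150 are enrolled in each. No other SD or margin for the CPSS appears in the article.

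**The concern.** One sentence gives the margin as a number of points and as a fraction of the SD, and with the stated SD these are different numbers. A third figure, the sample size said to follow from them, does not follow.

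The margin is what a non-inferiority comparison is judged against, and non-inferiority of T-CETA is a stated aim of the trial. If the upper confidence limit for the T-CETA deficit fell between 4.33 and 4.7 points, the result would pass by the number and fail by the rule offered to justify it. That choice should not be left open until data are in hand. The stated 80% power also depends on which margin, which SD and which sidedness are meant.

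**Working it through.** **Inputs.** SD = 13, margin M = 4.7, power 80%, alpha 0.05, equal arms, stated n = 114 per arm (Data analysis; Randomization and blinding). The true difference is not stated. I take it as 0, the usual assumption.

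**Formula.** n per arm = 2 × (z_alpha + z_beta)² × (SD/M)², with (1.645 + 0.842)² = 6.183 at one-sided 0.05 and (1.960 + 0.842)² = 7.849 at one-sided 0.025 (the same as a two-sided 95% interval). A t-based calculation was run as a check.

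**Step 1: the one-third claim.** 13/3 = 4.33. 4.7/13 = 0.36. 4.7 × 3 = 14.1. So 4.7 is one-third of 14.1, not of 13. The excess is 4.70 − 4.33 = 0.37 points, or 8.5%.

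**Step 2: reproduce 114 from the stated inputs.**
- One-sided 0.05: 2 × 6.183 × (13/4.7)² = 94.6, so 95 (t-based 95.3).
- One-sided 0.025: 2 × 7.849 × (13/4.7)² = 120.1, so 121 (t-based 121.1).

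Neither gives 114. Nor do 90% power at one-sided 0.05 (132) or an equivalence test at 0.05 (about 131).

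**Step 3: what does give 114.** Solving at one-sided 0.05: M/SD = √(2 × 6.183/114) = 0.329. Candidates near that ratio:

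| Margin | SD | n, normal | n, t-based |
|---|---|---|---|
| 4.33 | 13 | 111.3 | 112.0 |
| 4.3 | 13 | 113.0 | 113.7 |
| 4.7 | 14.1 | 111.3 | 112.0 |
| 4.7 | 14.2 | 112.9 | 113.6 |

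Rounded up, 4.3 with SD 13 gives 114 on both calculations, and 4.7 with SD 14.2 gives 114 on the t-based one.

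**Step 4: does the superiority figure settle the SD?** For an effect size of 0.5, alpha 0.025 and 80% power, the t-based n is 77.3, so 78, if alpha is two-sided. One-sided alpha gives 63.8, so 64. The stated 78 therefore reproduces as two-sided. It rests on a standardised effect, so it says nothing about whether the SD is 13.

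**Step 5: effect on the error rate if SD 13 is right and 4.7 is applied.** SE = 13 × √(2/114) = 1.722. At a true deficit of 4.33 and one-sided 0.05, P(pass) = Φ((4.70 − 4.33)/1.722 − 1.645) = Φ(0.213 − 1.645) = 0.076, against 0.05 with a margin of 4.33.

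**Step 6: power at 114 evaluable per arm, true difference 0.**

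| Margin | One-sided 0.05 | One-sided 0.025 |
|---|---|---|
| One-third SD (4.33 with SD 13, or 4.7 with SD 14.1) | 80.8% | 71.1% |
| 4.7 with SD 13, as written | 86.1% | 77.9% |

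**The case against.** The strongest objection is that the contradiction does not show which number is wrong. The figure of 114 and the one-third rule fix only the ratio of margin to SD. Nothing else in the paragraph uses SD 13, since the superiority calculation is standardised. The SD may be the misprint, with 4.7 a correct third of about 14.1. This stands. A reader might infer that the threshold is certainly looser than the plan's criterion, or that 4.3 is certainly the intended margin. The article supports neither without the condition that SD 13 is right.

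A reader might also infer that 114 can arise in only one way. It cannot be put so strongly. A true difference of about 0.4 points in favour of CETA, with margin 4.7 and SD 13, also gives about 114 at one-sided 0.05. So does margin 4.7 with an SD of 12.67 at one-sided 0.025. The article states neither assumption, and under both 4.7 is still not one-third of the SD.

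Third, sidedness. The two sample sizes use alpha in different senses, and it is tempting to call that an error. It is not: one-sided non-inferiority beside two-sided superiority is a conventional pairing, and an article may leave that wording to the full protocol or SAP. It matters here only because the stated power depends on it. The 71% figure applies to a one-third-SD margin with a 95% interval. On the margin and SD as written it would be 77.9%.

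Last, the effect is small, and 4.7 appears only in the sample-size paragraph. Both are true. That 4.7 will be the threshold in the analysis is an inference, though a natural one, as no other margin is given.

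**Conclusion.** The point holds as an inconsistency among four stated items: margin, SD, one-third rule and sample size. No reading tried makes all four true together, so the paragraph is wrong as written.

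The size is modest. If SD 13 is right, the margin is 0.37 points too wide by the plan's own rule, and the chance of passing at a true deficit of exactly one-third SD is about 7.6% rather than 5% (114 evaluable per arm, one-sided 0.05, normal approximation). If instead the SD used was about 14.1 to 14.2, the margin meets the rule and the SD is the figure to correct.

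The design size is not in question. A reader might infer that the trial is too small, but 114 per arm gives about 81% power for a one-third-SD margin at one-sided 0.05. The reservation is a two-sided 95% interval, where the same number gives about 71%. These powers assume no true difference between the CETA arms. Whether the SAP or the full protocol repeats 4.7 cannot be seen from the article.

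**What to change.** Before analysis, find the original calculation and make margin, SD and sample size agree.

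- If SD 13 stands, state the CPSS margin as 4.3 points (one-third of 13) and keep 114 per arm.
- If 4.7 was intended, correct the SD to the value used, about 14.1 to 14.2, and show the calculation.
- In either case, state that 114 per arm rests on a one-sided 5% test, that is, on the upper limit of a two-sided 90% confidence interval lying below the margin. If a two-sided 95% interval will be used instead, restate the power at 114 per arm as about 71%.
- Use the same margin in the full protocol and the SAP.

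The cost is one corrected number and one clarifying sentence. The 114 per arm and the total of 400 stay as they are, and no extra participants are needed.

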**Methods:**

This study is a hybrid type 1 three-arm randomized trial to be conducted in Lusaka, Zambia. Following an apprenticeship model, experienced non-professional counselors in Zambia will be trained as CETA trainers using a remote, technology-delivered training method. The new CETA trainers will subsequently facilitate technology-delivered trainings for a new cohort of counselors recruited from community-based partner organizations throughout Lusaka. AYA with mental and behavioral health problems seeking services at these same organizations will then be identified and randomized to (1) in-person CETA delivery, (2) telehealth-delivered CETA (T-CETA), or (3) treatment as usual (TAU). In the superiority design, CETA and T-CETA will be compared to TAU, and using a non-inferiority design, T-CETA will be compared to CETA, which is already evidence-based in other populations. At baseline, post-treatment (approximately 3–4 months post-baseline), and 6 months post-treatment (approximately 9 months post-baseline), we will assess the primary outcomes such as client trauma symptoms, internalizing symptoms, and externalizing behaviors and secondary outcomes such as client substance use, aggression, violence, and health utility. CETA trainer and counselor competency and cost-effectiveness will also be measured as secondary outcomes. Mixed methods interviews will be conducted with trainers, counselors, and AYA participants to explore the feasibility, acceptability, and sustainability of technology-delivered training and T-CETA provision in the Zambian context.

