#### Post-traumatic stress symptoms (Child PTSD Symptom Scale (CPSS) [74];)

The CPSS is a 17-item scale that corresponds to the DSM-5 criteria for PTSD on a 4-point Likert scale (*0 = not at all or only one time, 1 = once a week or less/once in a while, 2 = 2 to 4 times a week/half the time, 3 = 5 or more times a week/almost always*). The items produce a total Symptom Severity Scale. Based on our previous validity study in Zambia, an eligibility cutoff of ≥12 will be used [73].

Participants who do not meet the eligibility cutoffs on screening measures will exit the study and be provided resources for mental health and other social services in their area. Eligible AYA participants will continue to complete the second portion of the baseline assessment via the ACASI system, which includes measures of substance use, aggression/violence, functioning, and COVID-19 vaccine hesitancy (see the “Outcomes” section).

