The incremental cost-effectiveness analysis will compare the cost-effectiveness of CETA and T-CETA relative to TAU. We will first derive quality-adjusted life years (QALYs) from health utility reported at each follow-up time point by AYA and then estimate the differences in the mean QALYs gained per treatment condition over study follow-up using the mixed effects models detailed above. We will then divide incremental QALYs gained under CETA and T-CETA by the incremental cost of each relative to TAU from the economic perspective of the healthcare provider (i.e., payer’s perspective) to estimate the primary cost-effectiveness outcome: incremental cost per QALY gained. Sensitivity analyses will be undertaken to examine the uncertainty around the cost-effectiveness estimates, and further interpreted using cost-effectiveness acceptability curves that reveal to decision-makers the probability of the intervention being cost-effective compared to the alternative, given different (implicit monetary) values placed on incremental improvements in the outcome measurement and QALYs. Cost-effectiveness acceptability curves will be based on bootstrapped regressions (to account for non-normally distributed data) of the study group upon net benefits, controlling for clusters.

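### The QALY analysis as worded names no baseline utility and uses a group × time model that cannot be fitted to one total QALY per person

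*Protocol article*

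**What the plan says.** The cost-effectiveness paragraph of the Data analysis section will "derive quality-adjusted life years (QALYs) from health utility reported at each follow-up time point". It will then "estimate the differences in the mean QALYs gained per treatment condition over study follow-up using the mixed effects models detailed above".

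Those models are defined earlier in the same section: "Models will include fixed effects of treatment group, time, and a group × time interaction term". "Random effects will include client ID and counselor ID".

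The acceptability curves come from a different analysis, a bootstrapped regression of net benefit on study group that allows for clustering. No baseline utility term is named in either place.

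On data collection, the Methods part of the abstract gives the schedule as "At baseline, post-treatment (approximately 3–4 months post-baseline), and 6 months post-treatment (approximately 9 months post-baseline" months, and lists among the outcomes assessed then "secondary outcomes such as client substance use, aggression, violence, and health utility". In the body, the second part of the baseline assessment is one "which includes measures of substance use, aggression/violence, functioning, and COVID-19 vaccine hesitancy". The Outcomes section names the EQ-5D-Y as the utility instrument, without visit times of its own.

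**The concern.** The stated data source, quantity and model do not fit together on the ordinary reading. A QALY over follow-up is normally one accumulated total per person, whereas the model is built for repeated measurements. A reading that makes the model workable, with one QALY per interval, needs a utility at the start of the first interval, and the sentence names only follow-up utilities.

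Baseline utility matters in two separate ways:

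- **In the area.** It fixes the start of the utility curve. Without it the first 3–4 months, when treatment takes place, must be dropped or filled by a rule that is not given.
- **As a covariate.** It usually predicts later utility, so adjusting for it gains precision and removes the effect of a chance difference between arms at baseline.

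The QALY difference is likely to be small and enters the ratio that the protocol makes its primary cost-effectiveness outcome, so modest absolute errors can be large in relative terms.

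**Working it through.** The protocol gives no utility, QALY or cost figure, so there is nothing of its own to reproduce.

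**Inputs from the protocol.** Arms of 100 (TAU), 150 (CETA) and 150 (T-CETA); visits at 0, about 3–4 and about 9 months; the model terms above.

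**Assumptions, not in the protocol.** Utility SD 0.20; equal correlation r between visits, 0.3 to 0.7; true utility gain 0.05 at both follow-ups; no gain at baseline.

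**1. Can the model be fitted?** The fixed effects give six columns: intercept, two arm indicators, time, and two arm × time products.

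- One total per person: time is constant, and the design matrix has rank 3 of 6. Time and group × time are not estimable, and with one row per client the client effect cannot be separated from the residual.
- Two interval values per person: rank 6 of 6. The model can be fitted, but two intervals need three utilities, including baseline. The two follow-up visits alone bound only one interval.

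**2. Leaving baseline out of the area.** Times are in years and the trapezium rule is used. With visits at 0, t1 and t2, the true gain is 0.05 × [t2/2 + (t2 − t1)/2].

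| | t1 = 3 months, t2 = 9 | t1 = 4 months, t2 = 9 |
|---|---|---|
| Area from baseline | 0.05 × (0.375 + 0.250) = 0.0312 | 0.05 × (0.375 + 0.208) = 0.0292 |
| Time between follow-ups only | 0.05 × 0.500 = 0.0250 (−20%) | 0.05 × 0.417 = 0.0208 (−29%) |
| First follow-up carried back to 0 | 0.05 × 0.750 = 0.0375 (+20%) | 0.05 × 0.750 = 0.0375 (+29%) |

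**3. Not adjusting for baseline.** Take visits at 0, 3.5 and 9.5 months (six months after a 3.5-month visit).

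- Weights: 3.5/24 = 0.146, 9.5/24 = 0.396, 6/24 = 0.250. True gain: 0.05 × (0.396 + 0.250) = 0.0323.
- Standard error of the baseline difference: 0.20 × √(1/150 + 1/100) = 0.0258.
- Shift in the QALY difference from a one-standard-error imbalance: 0.0258 × (0.146 + 0.646r). This is 0.009 at r = 0.3 and 0.015 at r = 0.7, or 27% and 48% of the assumed gain.
- Variance removed by adjustment: (0.146 + 0.646r)² / (0.240 + 2r × 0.193). Here 0.240 is the sum of squared weights and 0.193 the sum of their pairwise products. At r = 0.3 this is 0.115/0.356 = 32%; at r = 0.7 it is 0.357/0.511 = 70%.

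**4. Check by simulation.** 4,000 trials of 100 vs 150, SD 0.20, r = 0.5, visits at 3.5 and 9 months, true difference 0.0302.

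| | Mean | Standard error | Mean when baseline favours CETA by more than 1 SE |
|---|---|---|---|
| Area, unadjusted | 0.0301 | 0.0162 | 0.0474 |
| Area, adjusted for baseline utility | 0.0302 | 0.0114 | 0.0300 |

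Both are unbiased on average. They differ in precision and in how they behave under chance imbalance.

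**The case against.** The strongest reply is that this is one sentence in a condensed article. It never says that each person contributes a single QALY; interval values fit the model, as would utilities modelled at all three visits and combined by area. The formula and the covariates usually sit in an analysis plan, which is not shown here.

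Much of that stands, and it rules out several stronger inferences:

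- **That baseline utility is excluded.** A reader might infer this from the reference to follow-up utilities. The protocol does not say so, and the abstract lists health utility among outcomes assessed at baseline.
- **That the group × time structure causes the baseline problem.** It does not. The two are separate: one is whether the model can be fitted, the other is the wording of the data source and the missing covariate.
- **That the cost-per-QALY result is biased.** Under randomisation an unadjusted difference is unbiased on average. Systematic error needs baseline to be left out of the area, and its direction then depends on how the first months are handled.
- **That the abstract and the baseline battery contradict each other.** The battery is an open list of domains, one of which (functioning) might cover the EQ-5D-Y, and the schedule figure is not available. This is a point to confirm, not a shown conflict.

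What does not fall away is that the paragraph states a method rather than leaving it open. It names the data, the quantity to be modelled (QALYs, not utilities) and the model. On the ordinary reading these cannot be combined. The readings that rescue it need a baseline utility that the sentence does not name. Nor does the argument that a repeated-measures model can carry baseline as a visit reach the net-benefit regression, which is a separate analysis.

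**Conclusion.** The point holds as a specification fault that should be corrected, in a secondary economic analysis. As worded, the model cannot be fitted to one total QALY per person, and fitting it to interval values requires a baseline utility that is not named. Neither the QALY analysis nor the net-benefit regression names adjustment for baseline utility, so the plan followed literally gives a less precise, and possibly incomplete, QALY difference.

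The sizes are illustrative. The variance reduction of about 32–70% depends on the correlation range and visit times, but not on the assumed SD or gain. The 20–29% under- or overstatement depends on visit timing and on an equal gain at both follow-ups. The 27–48% shift per standard error of imbalance also depends directly on the assumed gain and SD. None of these can be fixed from the protocol.

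**What to change.** 1. State that each person's QALY is the area under the utility curve from baseline through the last visit, and regress it on arm with baseline utility and site as covariates. Alternatively, model the utilities at all three visits with a common baseline mean across arms and combine the visit differences by area.
2. Add baseline utility as a covariate to the net-benefit regressions behind the acceptability curves.
3. Confirm that the EQ-5D-Y is in the baseline ACASI and name it in the Screening and baseline assessment section. A baseline utility that is not collected cannot be recovered later.

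The cost is a few sentences of wording and, only if the EQ-5D-Y is not already collected at baseline, one short questionnaire. Sample size and visit schedule do not change.

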## Discussion

Scalable systems of care, such as those being tested in this trial, are needed to close the mental health treatment gap in LMIC, particularly for populations at-risk for poor outcomes and low treatment adherence, such as adolescents and young adults. The need for telephone-based mental health services in LMIC has become widely discussed during the COVID-19 pandemic. Significant barriers to scale-up of evidence-based treatments in LMIC include a lack of feasible, sustainable training for local lay providers, and client access to care. This will be the first CETA trial that is specifically designed to evaluate the treatment effectiveness among an adolescent population and the first to feature a technology-based training modality and a telehealth delivery. This study is a first step to build a system of technology-driven training and treatment provision to expand access to evidence-based mental healthcare in Zambia and other LMIC settings. The need for effective, remotely delivered interventions is particularly relevant in the COVID-19 era.

There are several notable limitations to this study. First, this trial has a risk of social desirability bias in AYA reporting of symptoms, particularly in the CETA treatment arms given their therapeutic relationship with counselors. To combat this risk, we are using a standardized ACASI assessment system to measure symptoms at all time points, administered by research assistants and not by the counselors themselves. Second, this trial is occurring across several urban sites in the capital city of Zambia, and our participants will not be representative of AYA in more rural areas of Zambia and across other rural LMIC settings. Additional research will be needed on the delivery of these interventions to rural populations where T-CETA may actually be more feasible and acceptable because of access to private space and the high costs of transportation to a clinic.

If the CETA technology training platform is deemed feasible and comparably effective to in-person training models, and T-CETA is found to be as effective as in-person CETA for AYA in Zambia, we aim to expand these technology-driven, cost-effective training and treatment delivery methods across several contexts in sub-Saharan Africa and other LMIC globally.

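### The cost-effectiveness ratio is written upside down relative to the outcome it is meant to give; a T-CETA versus CETA economic contrast would be a cheap addition

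*Protocol article*

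**What the plan says.** The economic plan is one paragraph at the end of the Data analysis section of the protocol article. It opens by setting the comparison: "The incremental cost-effectiveness analysis will compare the cost-effectiveness of CETA and T-CETA relative to TAU". QALYs come from the health utility reports, and mean differences between conditions come from the mixed effects models. The ratio follows: "We will then divide incremental QALYs gained under CETA and T-CETA by the incremental cost of each relative to TAU". After naming the payer's perspective, the sentence states its aim: "to estimate the primary cost-effectiveness outcome: incremental cost per QALY gained".

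Uncertainty is handled by sensitivity analyses and acceptability curves. The curves are to show "the probability of the intervention being cost-effective compared to the alternative" and rest on bootstrapped regressions "of the study group upon net benefits, controlling for clusters".

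On clinical outcomes, the same section plans a head-to-head analysis of the two delivery modes: "Second, we will conduct a non-inferiority analysis in which we will compare the outcomes between the CETA and T-CETA groups". The last paragraph of the Discussion looks ahead to scale-up if T-CETA proves as effective as in-person CETA: "we aim to expand these technology-driven, cost-effective training and treatment delivery methods". The abstract lists cost-effectiveness among the secondary outcomes.

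**The concern.** The sentence that defines the ratio contradicts itself. The operation puts QALYs in the numerator and cost in the denominator; the name given to the result has them the other way round. The units differ, and so does the direction of benefit: a higher value is better under the written rule, a lower value under the named outcome. An analyst who followed the wording and kept the label would report a figure that cannot be compared with a willingness-to-pay threshold expressed as cost per QALY. This is the stated calculation for what the article itself calls the primary cost-effectiveness outcome, so it is not a detail left to a fuller document.

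A second, smaller matter is the comparator. The only one named for the ratios is TAU, whereas the title, the non-inferiority analysis and the scale-up aim all concern remote against in-person delivery. Two ratios against a shared comparator do not, by themselves, show what the dearer mode costs for each QALY it adds over the cheaper one.

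**Working it through.** The article gives no costs or QALYs, so there is no figure of the plan's own to reproduce. The first step is a check of units. The values in the later steps are assumptions, used only for illustration.

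**Step 1: units.** Let dC be the mean cost in an arm minus that in TAU, and dQ the same difference in mean QALYs.
- Operation as written: dQ / dC, in QALYs per unit of cost.
- Outcome as named: dC / dQ, in cost units per QALY.

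Each is the reciprocal of the other. No assumption is needed for this.

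**Step 2: size of the discrepancy (assumed dC of 50 to 200 and dQ of 0.02 to 0.05).**

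| dC | dQ | Written rule dQ/dC | Named outcome dC/dQ |
|---|---|---|---|
| 50 | 0.02 | 0.0004 | 2,500 |
| 50 | 0.05 | 0.001 | 1,000 |
| 100 | 0.02 | 0.0002 | 5,000 |
| 100 | 0.05 | 0.0005 | 2,000 |
| 200 | 0.02 | 0.0001 | 10,000 |
| 200 | 0.05 | 0.00025 | 4,000 |

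The written rule runs from 0.0001 to 0.001, and the named outcome from 1,000 to 10,000.

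**Step 3: does the inversion change the order of the arms?** Assume CETA has dC = 200 and dQ = 0.05, and T-CETA has dC = 100 and dQ = 0.04, both against TAU.
- Named outcome (lower is better): CETA 200/0.05 = 4,000; T-CETA 100/0.04 = 2,500. T-CETA ranks first.
- Written rule (higher is better): CETA 0.05/200 = 0.00025; T-CETA 0.04/100 = 0.0004. T-CETA ranks first.

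With positive increments the order is the same, provided each ratio is read in its own direction.

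**Step 4: do the acceptability curves depend on the ratio?** Incremental net benefit at a threshold L is L × dQ − dC. It is linear in cost and QALYs and contains no ratio, so the inverted sentence does not reach it.

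**Step 5: what the TAU-only ratios leave out.** With the Step 3 values, CETA against T-CETA is (200 − 100) / (0.05 − 0.04) = 100 / 0.01 = 10,000 per extra QALY. At an assumed threshold of 5,000:
- CETA against TAU: 5,000 × 0.05 − 200 = 50.
- T-CETA against TAU: 5,000 × 0.04 − 100 = 100.
- CETA against T-CETA: 50 − 100 = −50.

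Both modes pass against TAU, but CETA does not pass against T-CETA. If QALYs are instead equal at 0.05 and costs are 200 and 150, the ratios against TAU are 4,000 and 3,000, and CETA is dominated: it costs 50 more for no gain. In both cases the answer follows from the planned increments by subtraction, but not from the two ratios alone.

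**The case against.** On the ratio, the fair defence is that this is a drafting slip. The outcome is correctly named in the same sentence, a competent health economist would compute cost per QALY, and a value such as 0.0005 offered as a cost per QALY would be noticed at once. The curves that inform the decision rest on net benefit, cost-effectiveness is a secondary outcome, and nothing in the sample size, error rates or data collection is touched. All of that stands and limits the severity. It does not make the sentence right.

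A reader might infer that the inversion would reverse the ranking of CETA and T-CETA. The article does not support that: for positive increments the two ratios order the arms identically. A reversal needs someone to compute QALYs per unit of cost and then read it as cost per QALY.

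On the comparator, a reader might infer that T-CETA is never compared with CETA in economic terms, or that the analysis cannot say which mode to scale up. Both go too far. The curves refer to an unnamed alternative, and the regressor is study group in a three-arm trial, so the model can yield the contrast. The planned increments share a comparator, so the point difference follows by subtraction. The article is also a condensed account: it says the full protocol is available on request, and the list of economic contrasts may well be there. What remains is that the article fixes TAU as the comparator for the ratios and does not commit to the other contrast.

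**Conclusion.** The inverted ratio is an error, established from the text without any assumed figure: the written operation is the reciprocal of the named outcome and cannot be set against a cost-per-QALY threshold. It is a minor-to-moderate correction to a secondary outcome. The acceptability curves are unaffected, and the order of the arms holds if increments are positive and the ratio is read in its own direction.

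The T-CETA versus CETA economic contrast is a suggested improvement, not a second error. Its case rests on the mismatch between the comparator named for the ratios and the in-person versus remote question that the trial also poses. All cost, QALY and threshold values above are assumptions; they show the form of the problem and predict nothing about this trial.

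**What to change.** Correct the ratio: for each CETA arm, (mean cost in arm minus mean cost in TAU) / (mean QALYs in arm minus mean QALYs in TAU). This is a change of wording only and costs nothing.

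As an inexpensive addition, state that T-CETA versus CETA will also be reported as incremental cost, incremental QALYs and incremental net benefit, from the same bootstrapped net-benefit regression. Subtraction already gives the point estimate; naming the contrast ensures that its uncertainty is reported too. It uses the cost and EQ-5D-Y data already planned, with no extra participants or assessments. The downside is one more contrast, which may be imprecise and should be presented with that caution.
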